## Abstract

**Background:**

There is increasing scientific knowledge about the interaction between physiological (musculoskeletal, neuromuscular, cognitive and sensory) systems and their influence on balance and walking impairments in Parkinson’s disease. We have developed a new conceptual framework for balance training, emphasising specific components of balance control related to Parkinson’s disease symptoms by using highly challenging, progressive and varying training conditions. The primary aim of this proposed randomised controlled trial will be to investigate the short-term and long-term effects of a 10-week balance training regime in elderly with Parkinson’s disease.

**Methods/Design:**

Eighty participants with mild to moderate idiopathic Parkinson’s disease will be recruited and randomly allocated to an intervention group receiving balance training or a control group whose participants will continue to receive their usual care. The intervention will consist of a 10-week group training regime (1-hour training, three times per week), which will be led by two physiotherapists to ensure training progression and safety. The conceptual framework will be applied by addressing specific balance components (sensory integration, anticipatory postural adjustments, motor agility, stability limits) through varying training conditions and structured progression. Assessment will be conducted through a multi-dimensional battery of outcomes, prior to and immediately after the 10-week intervention, and at 9 and 15 months’ follow-up after entering the study. Primary outcome measures will be balance performance (assessed using the Mini Balance Evaluation Systems Test), change in gait velocity (m/s) between single and dual task walking, and fear of falling (evaluated using the Fall Efficacy Scale International).

**Discussion:**

This study has the potential to provide new insight and knowledge of the effects of specific, varied and challenging balance training on a wide health spectrum in elderly with PD. If found to be effective, this pragmatic approach with translation of theory into practice, can be implemented in existing outpatient care.

**Trial registration:**

NCT01417598

## Background

Parkinson’s disease (PD) is a major worldwide health problem
[1], with a reported incidence rate ranging from 11 to 19/100,000 per year in the European population
[2]. Balance and walking impairments are present even in the early stages of PD
[3-6] and have been shown to be associated with restrictions in everyday activities
[7] and reduced quality of life (QoL)
[8].

Furthermore, elderly with PD have shown reduced levels of physical activity
[9] and a nine times increased risk of injurious falls, compared with the healthy elderly
[10]. As PD progresses, balance problems gradually increase and are generally non-responsive to or worsen with levodopa treatment
[11-13]. Currently, there is a growing body of research that highlights the role of physical exercise as an essential part of managing the disease, with potential neuroprotective mechanisms
[14,15]. The effects of balance training on balance and gait performance are promising for individuals with PD
[16-18], although several questions remain unanswered, particularly regarding dose, intensity and duration, as well as regarding specific exercises to improve balance control in the different stages of the disease
[17-21]. Additionally, there is a lack of knowledge of the long-term effects of training interventions on participation in everyday living, such as physical activity and QoL
[16].

Balance control relies on the interaction of several physiological systems (the musculoskeletal, neuromuscular, cognitive and sensory systems) with environmental factors and the performed task
[22]. Balance impairment or postural instability in individuals with PD is often associated with poor or absent *reactive responses* following external perturbations, such as performing a rapid step following a slip or trip
[23]. However, as degeneration of the basal ganglia affects many physiological systems essential for balance control, balance disorders in PD cannot be addressed to one single function but, rather, are the result of impairments of multiple systems
[24-26]. First of all, dysfunction of the basal ganglia influences *sensory integration*, i.e. the ability of the central nervous system to transform different modalities of sensory information (somatosensory, visual and vestibular) into a single reference frame, which is important for estimation of limb and body position in relation to the environment
[27]. Particularly, individuals with PD have shown impaired proprioception
[13,27], overestimation of the amplitude of movements
[28] and over-reliance on vision for balance control
[29]. Moreover, the central motor drive has shown to be impaired in PD
[30], causing bradykinetic movements and poorly timed and scaled *anticipatory postural adjustments* (APAs), i.e. feedforward control to stabilise the posture before and during voluntary movements
[31,32]. Furthermore, the PD-characteristic “stooped” posture, decreased joint range of motion, narrow foot stance and axial rigidity increase the risk of instability since these musculoskeletal constraints reduce the *functional limits of stability*, i.e. the area in which the body centre of mass (CoM) can be moved with maintained stability and without changing the base of support (BoS)
[33,34]. Taken together, sensory-motor interaction is essential for balance control and consequently, as discussed by Konczak et al.
[27], sensory problems may degrade movement responses and cause instability to individuals with PD.

The functions of the basal ganglia incorporate motor program selection and adaptation
[35,36], here referred to as *motor agility*, which involves maintenance of coordination between body parts, task-specific adjustments of movement and quick shifts from one task to the next. Deficient motor regulation in PD, manifested as poor inter-segmental coordination
[37], problems adopting postural synergies
[35,38] and delayed change of motor commands when shifting from one task to another
[39], is believed to contribute to increased instability and freezing of gait during fall-related activities
[40,41]. Another critical aspect of balance control in PD is the ability to divide attention and simultaneously process multiple tasks (motor or cognitive), i.e. *multi-tasking.* While performing a multi-task activity, individuals with PD compared with healthy subjects are more inclined to shift attention away from the balance task, which can lead to falls
[24].

To be successful, all types of training require the application of basic training principles of (i) *specificit*y, i.e. being specific to the targeted function; (ii) *progressive overload*, i.e. providing a challenging overload to the physiological system through a certain level of intensity and regularity; and (iii) *varied practice*, i.e. promoting variation between exercise conditions
[42,43]. To be specific, balance training needs to target functions, or impairments, of balance control associated with PD symptoms. As previously mentioned, there is increasing scientific knowledge concerning the interaction between and impact of different physiological systems for balance disorders in PD
[24-26]. Previous intervention studies targeting balance performance in PD have, however, mainly emphasised non-specific training or compensatory training
[17,44]. Moreover, to stimulate relearning of physiological systems important for balance control, the challenge level (i.e. intensity of the training, the difficulty level of balance exercises and the total training dose) needs to be considered. Allen et al.
[17] recently concluded, based on a meta-analysis of exercise interventions targeting balance performance in PD, that previous studies in general have used low challenge levels, suggesting that future exercise interventions should focus on more challenging aspects of balance exercises and a higher training dose. Furthermore, to enhance generalisation of learned motor skills to a wide variety of situations and promote a multi-faceted repertoire of movement strategies, it is essential to guarantee practice through a wide variety of balance exercise conditions
[43].

We hypothesise that a new conceptual framework for balance training, emphasising critical aspects of balance control specifically related to PD symptoms through highly challenging, progressive and varied exercises, will improve, or maintain, balance and gait performance in elderly with PD. Moreover, we predict that increased physical functioning following training will lead to greater confidence in everyday participation, improved QoL and increased levels of physical activity.

The primary aim of this proposed randomised controlled trial will be to expose elderly individuals with mild to moderate PD to a 10-week balance training regime, and compare the efficacy of balance training to care as usual using laboratory, clinical, free-living and self-perceived assessments before and immediately after the intervention as well as 9 and 15 months post-baseline.

## Methods

### Design

In a prospective, randomised controlled clinical trial, with 9 and 15 months’ post-baseline follow-up, 80 elderly patients with PD living in Stockholm County, Sweden, will be included. The project has been approved by the Regional Board of Ethics in Stockholm (Dnr: 2009/819-32 and 2010/1472-32).

### Participant selection

Community-dwelling individuals with PD will be recruited from Karolinska University Hospital, the Swedish Parkinson Associations and outpatient neurological clinics as well as by physicians with a specialty in neurology in Stockholm County. Advertisements in local newspapers will also be used to recruit participants. Potential participants will receive written information about the aims of the study and its procedure, with an invitation to indicate their interest in participating to the study coordinator. Inclusion criteria will be a clinical diagnosis of “idiopathic” PD, according to the Queens Square Brain Bank criteria, ≥60 years of age, have adapted to their present PD-medication and the ability to independently ambulate indoors without a walking aid. We will include mild to moderate PD (Hoehn and Yahr scores II and III)
[45], since physical group training has been proved feasible for this level of disease severity
[46,47]. Exclusion criteria will be a history suggesting “atypical” PD symptoms, as defined by Hughes et al.
[48], a Mini-Mental State Examination (MMSE) score ≤24
[49] and other existing neuromuscular disorders or medical conditions that substantially influences their gait and balance performance or their participation in the training program. To screen potential participants’ eligibility, a physiotherapist will conduct a telephone interview based on a clinical self-report form covering questions about personal and medical history and self-perceived balance performance.

### Randomisation

Participants will be divided into two geographic cohorts (south and north) to reduce the travelling time for the participants. After baseline assessments, the participants in each cohort will be randomly assigned to two different groups in blocks of four, one experimental group with balance training and one control group. The sequence of allocation will be performed using web-based software and will be concealed to the participants and testers until the baseline measurement is completed. Blinding of group allocation will, however, not be possible since the test leaders will be supervising the training intervention (as described below).

### Intervention group

We have applied the training principles of specificity, varied practice and progressive overload to design a conceptual framework for balance training in PD. The framework comprises specific exercises associated with balance and walking constraints in PD (Table
1). The intervention period is divided into three blocks (A, B and C) to promote appropriate progressive overload through the course of training (Table
2). Implementation of the training principles for balance training and motor learning is outlined below.

**Table 1 T1:** **Parkinson’s disease (PD) specific****balance components, constraints affecting****balance and exercises designed****to reduce these constraints**

**Balance components**	**Constraints in PD**	**Exercise principles**	**Exercise objectives**
**SENSORY INTEGRATION**			
Integration of sensory information (somatosensory, visual and vestibular) for estimation of body position	- Impaired somatosensory integration	Walking tasks on varying surface with or without visual constraints	Improve interpretation of and reliance on somatosensory information
	- Poor proprioception		
	- Visual dependency		
**APAs**			
Prediction and control of perturbation related to voluntary movements	- Poorly timed and scaled APAs	Voluntary arm/leg/trunk movements focusing on movement velocity and amplitude, and postural transitions	Improve APA strategies regarding quality (timing, amplitude) and task- specific adaptation
	- Bradykinesia		
**MOTOR AGILITY**			
Coordination between body parts and movement adaptation, e.g. regulation of movement and quick shifts between tasks	- Bradykinesia	Whole-body coordination during varying gait conditions and reciprocal movements. Quick shifts of movement characteristics (velocity, amplitude and direction) during predictable and unpredictable conditions	Improve whole-body coordination, ability to adapt movement and quick shifts between different tasks
	- Impaired whole-body coordination		
	- Biomechanical constraints		
	- Inflexible motor programming		
**STABILITY LIMITS**			
Whole-body regulation relative to the BoS	- Reduced functional stability limits	Voluntary leaning tasks in standing with varying BoS-stimulating weight shifts in multiple directions through arm and trunk movements	Improve the ability to safely control CoM within BoS to increase functional limits of stability
	- Biomechanical constraints		
	- Poor proprioception		
	- Impaired somatosensory integration		

APAs = anticipatory postural adjustments; BoS = base of support; CoM = centre of mass.

**Table 2 T2:** Training progression

**Training principles and objectives**		**Week**	**Balance components**	**Multi-task**
**A**	Introduction of performance of each balance component separately and emphasizing quality of performance to accomplish familiarity and task-specific motor learning.	**1**	Motor agility/stability limits	
		**2**	Sensory integration/APAs	
**B**	Improvement of balance performance and strategies of attention in varying balance conditions through increased level of difficulty and task variation for each balance component separately, and by using multi-tasking (i.e. cognitive or motor secondary task).	**3**	Motor agility/stability limits	C-DT
		**4**	Sensory integration/APAs	M-DT
		**5**	Motor agility/stability limits	C-DT
		**6**	Sensory integration/APAs	M-DT
**C**	Further challenging of movement complexity through increased levels of difficulty, task variation by successively integrating the balance components, and increasing demands of multi-tasking (i.e. cognitive and motor secondary tasks are performed simultaneously).	**7**	Sensory integration/APAs/motor agility/stability limits	C + M-DT
		**8**	Sensory integration/APAs/motor agility/stability limits	C + M-DT
		**9**	Sensory integration/APAs/motor agility/stability limits	C + M-DT
		**10**	Sensory integration/APAs/motor agility/stability limits	C + M-DT

The balance program divided into three blocks (Blocks A-C), with training principles and objectives for each block.

APAs = anticipatory postural adjustments; C-DT = cognitive dual-task training; M-DT = motor dual-task training; C + M-DT = mixed cognitive and motor dual-task training.

#### *Specificit*y

In contrast to non-specific training in PD
[17], King and Horak
[25] recently proposed a symptom-specific training approach targeting particular mobility impairments in individuals with PD. Our approach towards balance training resembles theirs regarding the principle of specificity. In the proposed intervention, we will use four balance components (sensory integration, APAs, motor agility, and stability limits) to target symptom-specific balance impairments associated with instability and falls in PD (see Table
1). The applications of these balance components will be separated according to exercise principles and objectives.

#### Varied practice

Through the course of training, exercise variation will be emphasised to enhance motor learning and promote generalisation of balance skills to everyday activities
[43]. Based on previous findings, individuals with PD, compared with healthy individuals, need more time to achieve motor learning
[50,51]. Therefore, as illustrated in Table
2, variation in the training will be increased successively through the course of training. During the initial phase of training (Block A), the exercise for each balance component will be trained separately in blocks on a weekly basis, to encourage familiarity of the principles and objectives and promote task-specific motor learning. In the later phases of training (Blocks B and C), generalisation of motor skills will be facilitated by increasing training variation with regard to characteristics of exercise in each balance component (e.g. variation in terms of body position, BoS and movement direction/velocity/amplitude) in Block B, and by integrating exercises from different balance components in Block C. In addition, multi-task exercises in Blocks B and C will further increase training variation (see Table
2).

#### Progressive overload

Based on previous recommendations
[17] and national guidelines for physical training
[52], as well as our experience from a pilot study of balance training in PD (data not yet published) and balance training in elderly
[53], we believe that the training frequency, duration and total training dose planned for use in the proposed study (three 1-hour sessions/week during 10 weeks) will be sufficient to improve balance performance in elderly with mild to moderate PD. To achieve optimised challenges to individual capacities, the physiotherapists will individually adjust the difficulty level of the exercises for each balance component as follows:

*Sensory integration:* increased surface unevenness and restricted field of vision (vision-restricting glasses, carrying an object)

*APAs:* increased movement amplitude and velocity

*Motor agility:* increased gait complexity (e.g. altering velocity, step patterns, etc.), increased gait demands according to planned (awareness of upcoming sequences/tasks) and unplanned shifts upon verbal commands (unawareness of upcoming sequences/tasks) between different gait conditions, reciprocal movements and walking directions

*Stability limits:* changing the area or condition of the BoS and increasing leaning movement amplitude

Intermittent presence of reactive postural adjustments will be used as an indicator of the appropriate difficulty level. To target multi-task performance in PD, cognitive (e.g. counting, remembering items/numbers) and secondary motor tasks (e.g. carrying and/or manipulating objects)
[54], will be introduced in Block B and further progressed in Block C (see Table
2). Multi-task training will be individually adjusted for each participant. The level of difficulty for the secondary tasks (motor or cognitive) will be considered appropriate if the primary task is affected (e.g. decreased gait velocity or increased stride variation). Moreover, as described above, training demands will additionally be challenged by increasing variation through the course of the program.

#### Feedback

In individuals with PD, goal-oriented oral feedback that addresses information externally to the body, i.e. concerning the performance of the task in relation to the environment (rather than the position or motion of the body), has been reported to enhance walking
[55] and balance performance
[56]. In the proposed trial, oral feedback will be as simple as possible and be externally oriented to promote movement automaticity. Cueing strategies (visual or oral), as described by Nieuwboer et al.
[57], will be used when needed for participants experiencing severe freezing through the course of training; however, they will not be used as a standard training component.

#### Training/intervention procedure

The balance training will be performed in groups of five to seven participants in the facilities of the Physiotherapy Clinic at Karolinska University Hospital. To secure progression and safety, all training sessions will be led by two physiotherapists with experience of working with PD and elderly patients. To standardise the intervention and secure adherence to the proposed theoretical framework, all physiotherapists will participate in a theoretical and practical workshop before the intervention starts and will be supervised during the course of the training.

Every training session will start with a warm-up session for 5 min, consisting of varied walking tasks aiming to boost the cardiovascular system. The following 50 min (short rests included) will focus on highly challenging exercise blocks (approximately 10 min per block) of standing and walking conditions. The balance components of stability limits and APAs will mainly be addressed through standing exercises, and the balance components of motor agility and sensory integration will mainly be addressed in walking exercise conditions.

The program will end with a 5-min cool-down session with slow walking, axial stretching and breathing exercises. The number of exercise blocks for each training occasion and the distribution between standing and walking exercises will be adjusted to the level of ability in each group. After each training occasion, individuals’ performance of the exercises included will be briefly documented, as an evaluation of both the appropriateness of exercises and the current level of difficulty. Adverse events (defined as an injury or medical event that restricts everyday activities and participation in the intervention) and training adherence will be monitored and recorded
[58].

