### Sample size

The sample size for this study was determined from a pilot study (not yet published), including five mild to moderate PD subjects who participated in the proposed balance training, and also from previous trials on patients with PD and elderly people
[53,73,74]. For each sample size calculation, power was set at 80% and a two-sided test at the alpha level of 5%. For the Mini-BESTest, a sample size of 24 was required to detect a 3-point difference between groups, assuming a mean variance or standard deviation (SD) of 3.6 (effect size: 0.83). For the interference effect of dual task performance, i.e. percent change in gait velocity (m/s) between single and dual task walking
[74], a sample size of 27 subjects was required to detect a difference of 10% (SD 13) between groups (effect size = 0.77). Finally, for the FES- I, a sample size of 32 subjects was required to detect a difference of 2 points (SD 2.8) between groups (effect size = 0.71). The dropout rate was set at 15%, corresponding to intervention studies with PD subjects
[75,76]. Taken together, to ensure adequate statistical power the sample size for this study would optimally be 40 per group (total n = 80).

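### The sample size makes no allowance for clustering by training group in the intervention arm, and no training-group effect is named in the model; FES-I has little power to spare

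*Protocol article*

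**What the plan says.** Under Training/intervention procedure, "The balance training will be performed in groups of five to seven participants". The same section says that the number of exercise blocks and the balance of standing and walking work "will be adjusted to the level of ability in each group". Two physiotherapists lead every session. Under Exercise on prescription, the closing discussion of physical activity is also held as a group. Under Randomisation, allocation is by individual, in blocks of four within two geographic cohorts. Under Control group, the comparison arm receives usual care and is not grouped.

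The Sample size section states that "power was set at 80% and a two-sided test at the alpha level of 5" per cent, and gives three calculations:

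- Mini-BESTest: "a sample size of 24 was required to detect a 3-point difference between groups, assuming a mean variance or standard deviation (SD) of 3.6".
- Dual-task interference: "a sample size of 27 subjects was required to detect a difference of 10% (SD 13) between groups".
- FES-I: "a sample size of 32 subjects was required to detect a difference of 2 points (SD 2.8) between groups".

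The one inflation is for attrition: "The dropout rate was set at 15" per cent. The section concludes that "to ensure adequate statistical power the sample size for this study would optimally be 40 per group (total n = 80").

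The Statistical analysis section plans mixed models where appropriate. It does not say which random effects they contain.

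**The concern.** Forty people trained five to seven at a time form about 6 to 8 groups (40/7 = 5.7, 40/5 = 8). Members of a group share sessions, peers and a group-specific mix of exercises, so their outcomes may be correlated. Controls have no such structure. If the correlation is positive, the intervention-arm mean is less precise than 40 independent observations would make it.

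Two things are at stake. If training group is left out of the model, confidence intervals are too narrow and the nominal 5% test rejects too often. If it is included, type I error is protected, but power is lower than the Sample size section implies. FES-I is the outcome that drives the sample size, so it has the least room to absorb this.

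**Working it through.** **1. Reproduce the plan's figures.** For two independent samples, n per arm = 2(1.96 + 0.84)² / d², with d = difference/SD.

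- Mini-BESTest: d = 3/3.6 = 0.833, n = 22.6, so 23 (exact t: 24; stated 24).
- Dual task: d = 10/13 = 0.769, n = 26.5, so 27 (exact t: 28; stated 27).
- FES-I: d = 2/2.8 = 0.714, n = 30.8, so 31 (exact t: 32; stated 32).

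The stated figures are per-arm numbers for independent observations. Dropout: 32/0.85 = 37.6, so 38 per arm against 40 planned. That leaves two spare per arm for FES-I.

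**2. Inputs for the clustered calculation.** Evaluable per arm: 40 × 0.85 = 34. Evaluable per training group (m): 6 × 0.85 = 5.1 for groups of six, and 7 × 0.85 = 5.95, taken as 6, for groups of seven. The ICC is my assumption, because the article gives none; I show 0.02, 0.05 and 0.10.

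**3. Formulas.** Design effect in the intervention arm only: DE = 1 + (m − 1) × ICC. In SD units, SE = √((DE + 1)/34). The ratio of true to naive SE is √((DE + 1)/2). Type I error if group is ignored is 2 × [1 − Φ(1.96/ratio)]. Power by normal approximation is Φ(d/SE − 1.96). The group-based version uses a noncentral t with Satterthwaite degrees of freedom, df = (v1 + v2)² / [v1²/(k − 1) + v2²/33], where v1 = DE/34, v2 = 1/34 and k = 34/m groups.

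**4. One case in full (FES-I, m = 5.1, ICC 0.05).** DE = 1 + 4.1 × 0.05 = 1.205. SE = √(2.205/34) = 0.2547. d/SE = 0.7143/0.2547 = 2.805. Normal power = Φ(0.845) = 80%. With k = 6.67, df = 17.0, critical t = 2.11 and power = 75%. SE ratio = √(2.205/2) = 1.05; type I error = 6.2%.

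**5. Results** (each range runs over m = 5.1 and m = 6):

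| ICC | SE ratio | Type I error if group omitted | FES-I power, normal | FES-I power, group-based df |
|---|---|---|---|---|
| 0.02 | 1.02 | 5.5-5.6% | 82% | 77-78% |
| 0.05 | 1.05-1.06 | 6.2-6.5% | 79-80% | 73-75% |
| 0.10 | 1.10-1.12 | 7.4-8.0% | 75-77% | 68-71% |

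The FES-I reference with no clustering and 34 per arm is 83% (t, 66 df) or 84% (normal). Groups of five (4.25 evaluable) do slightly better: 83%, 81% and 78% (normal), or 79%, 77% and 74% (group-based df).

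**6. The other primary outcomes.** Dual task starts at 88%. At ICC 0.05 it is 85-86% (normal) or 79-81% (group-based df); at ICC 0.10 it is 81-82% or 74-77%. Mini-BESTest starts at 92%. At ICC 0.10 it is 87-88% or 81-83%.

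**7. Interval width.** Relative to an ordinary t interval (critical value 2.00), the group-based interval is wider by SE ratio × critical t / 2.00: 7-9% at ICC 0.02, 11-14% at 0.05 and 17-22% at 0.10. For example, 1.118 × 2.175/2.00 = 1.22.

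**The case against.** The strongest reply is that the article does not show the analysis ignoring training group. A reader might infer that it treats intervention participants as independent, but the Statistical analysis section names mixed models without their random effects. It neither includes nor excludes training group, and that detail may sit in an analysis plan that is not shown. This stands: the SE and type I consequences hold only if group is omitted and the ICC is positive. It does not rescue the Sample size section, whose calculation is stated and assumes independence. Including the group effect would cost power that was not budgeted.

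Second, a reader might suppose that each group has its own therapists. The text says only that two physiotherapists lead each session; it does not say whether they work across groups. All attend one workshop and are supervised. Under Progressive overload, difficulty and multi-task load are adjusted for each individual, which works against similarity within groups. This stands as a reason to include low ICCs in the range. It does not remove the group-level content or the shared sessions.

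Third, it is tempting to say that 80% power is simply not delivered. That is too strong. By normal approximation FES-I holds 80% up to an ICC of about 0.05, and Mini-BESTest holds it throughout the range. With group-based degrees of freedom FES-I is already at 79-80% at ICC 0, so part of the loss is the price of estimating a variance from few groups and not of clustering itself.

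**Conclusion.** The point holds for the sample size and is conditional for the analysis. The article fixes a partially nested design and sizes it as if all observations were independent, with two participants per arm to spare on FES-I. Over an assumed ICC of 0.02 to 0.10, FES-I falls below 80% from an ICC of about 0.05 (normal approximation), or throughout that range with group-based degrees of freedom. Dual task is borderline at 0.10, and Mini-BESTest is secure. The effect is moderate and rests on an ICC that the document does not supply. It warrants correction but does not undermine the trial.

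**What to change.** - Record a training-group identifier for every intervention participant from the start. It is hard to reconstruct later.
- Specify in the mixed model a training-group random effect in the intervention arm only, with each control as its own cluster, and Satterthwaite or Kenward-Roger degrees of freedom.
- Restate power in the Sample size section at n = 80 for groups of five to seven over ICC 0.02 to 0.10, marking the ICC as an assumption.

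No extra participants are needed for this. Holding 80% for FES-I by enlarging the trial would be a separate decision: with six per group, 32 × (1 + DE)/2 / 0.85 gives 43 per arm at ICC 0.05 (DE 1.25) and 48 at ICC 0.10 (DE 1.5).

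The cost is one model term, one data field, the interval widening shown above, and a less favourable power statement for FES-I. With only 6 to 8 groups the between-group variance will be poorly estimated, so the small-sample degrees of freedom should be fixed in advance.
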